#### Secondary endpoints

Erythrocyte sedimentation rate (ESR), C-reactive protein, procalcitonin, SII [17], coagulation function (prothrombin time, activated partial prothrombin time, bleeding time), liver function (alanine transaminase, glutamic transaminase, lactate dehydrogenase, total bilirubin, direct bilirubin), renal function (creatinine, uric acid, eGFR), high-sensitivity troponin T, serum B-type natriuretic peptide, myocardial enzyme (creatine kinase, creatine kinase MB isoenzyme), and other laboratory examination of blood;Chest X-ray (for pulmonary inflammation and effusion, etc.), CTA scan of the cervical, thoracic, and abdominal aorta artery (for aortic diameter and extent of dissection, etc.), cardiac ultrasound (for cardiac ejection fraction and left ventricular diastolic dysfunction, etc.), and other imaging examinations.The patient’s cardiopulmonary bypass time during surgery, total surgical time, aortic cross-clamping time, and postoperative hospital stay;Postoperative drainage color, drainage volume, postoperative patient blood transfusion, and transfusion volume;The incidence of postoperative sternal infection, secondary debridement, secondary tracheal intubation, pneumonia, and delirium; andEnzyme-linked immunosorbent assay (ELISA) will be performed to detect and measure IL-1β IL-2, IL-4, IL-6, IL-8, IL-10, IL-12, IL-13, TNF-α, INF-γ, granulocyte–macrophage colony-stimulating factor (GM-CSF) and calcitonin;

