### Sample size {14}

The required sample size was calculated using the PASS (15.0.5) software. The primary endpoint of efficacy was used to calculate the sample size. In the literature, the total death rate of hospitalization after surgery was 25% [7], the incidence of organ malperfusion syndrome was 15–33% [19, 20], permanent dialysis was 2.6% [21], tracheotomy was 8% [22], neurological impairment was 6.9% [22], postoperative mechanical circulatory support was 20% [23], unplanned cardiac reoperation was 4.2% [24], and postoperative cardiac arrest was 0.7–5.2% [25]. Therefore, we assumed that the incidence of composite endpoint events in the control group is 70%, and the incidence of composite endpoint events in the ketorolac group is reduced to 40%. Using PASS (15.0.5) software, when the sample size of the ketorolac group and the control group is 53 cases, this difference can be detected with over 90% confidence. Considering that the loss of follow-up rate is higher than 10%, the final total sample size of this experiment is 120 cases, with 60 cases in the experimental group and 60 cases in the control group.

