## Statistical methods

### Statistical methods for primary and secondary outcomes {20a}

Statistical analysis will be performed using SPSS software (version 26.0) and R (× 64 3.5.0). Continuous variables will be presented as mean ± standard deviation. The Kolmogorov–Smirnov test will assess normal distribution. If variables exhibit normal distribution, an independent sample *t*-test will be employed; otherwise, the Mann–Whitney *U* test will be utilized. Categorical variables’ frequency will be expressed as percentages and analyzed using the chi-square test or Fisher’s exact test. It should be noted that we are not conducting an Intention to Treat analysis due to the exclusion of patients with more than 10% missing data. Double-tailed *p*-values and 95% confidence intervals will be reported, with statistical significance defined as *p* < 0.05.

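### Re-intubation, delirium, sternal infection and debridement are compared as plain percentages although early death or continued ventilation can prevent them, which can bias these secondary comparisons against ketorolac

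*Protocol article*

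**What the plan says.** The Secondary endpoints section of the protocol article includes "The incidence of postoperative sternal infection, secondary debridement, secondary tracheal intubation, pneumonia, and delirium". It attaches no at-risk population to these items.

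Statistical methods {20a} fixes the comparison: "Categorical variables’ frequency will be expressed as percentages and analyzed using the chi-square test or Fisher’s exact test". The same section says that no intention-to-treat analysis will be done, because patients with more than 10% missing data are excluded. Section {20c} repeats that such patients are deleted.

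Sample size {14} gives the rates on which the trial is planned: "the total death rate of hospitalization after surgery was 25" per cent, with tracheotomy at 8% and neurological impairment at 6.9%. For the composite, "we assumed that the incidence of composite endpoint events in the control group is 70" per cent, and "the incidence of composite endpoint events in the ketorolac group is reduced to 40" per cent. Death, tracheotomy and neurological impairment are all components of the primary efficacy endpoint.

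**The concern.** Re-intubation needs a first extubation. A patient who dies on the ventilator, or goes to tracheotomy without ever being extubated, cannot have it. Delirium cannot be scored in a patient who dies before waking or is never assessable. Sternal infection and debridement usually arise some days after surgery, so an early death prevents them too.

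The stated rules leave two routes for these patients:

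- They stay in the denominator without an event. They then count the same as a full recovery.
- They are deleted for missing data. The comparison is then restricted to a group selected after randomisation by outcomes that the drug is meant to change.

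On the first route, a drug that prevents early deaths exposes more of its patients to these complications. The chi-square test then mixes the effect on survival with the effect on the complication, and it can show a spurious excess or hide part of a real reduction. The artefact grows with the true survival benefit.

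**Working it through.** **Design figures.** The sample size reproduces, which confirms 70% and 40% as the planning rates. With unpooled variance, two-sided alpha 0.05 and 90% power, n = (1.960 + 1.282)² × (0.7×0.3 + 0.4×0.6) / 0.3² = 52.5, so 53 per arm (power 90.2%). Then 53 / 0.9 = 58.9, and the plan takes 60.

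**Inputs for the bias.** Control rates from {14}: death 0.25, tracheotomy 0.08, neurological impairment 0.069. Planned ratio: 40/70 = 0.571.

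**Assumptions, not in the documents:**

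- The ratio applies to each component. Ketorolac rates are then 0.143, 0.046 and 0.039.
- Death and the second event are independent.
- A share f of deaths comes before the complication could occur.
- All tracheotomies preclude re-intubation, and all neurological impairment precludes delirium assessment.
- The drug has no effect on the complication among patients who can have it.
- Patients who cannot have the event are counted as event-free.

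**Formula.** Fraction able to have the event = (1 − f × death) × (1 − e). Here e is tracheotomy for re-intubation, neurological impairment for delirium, and 0 for sternal infection and debridement. The risk among those able to have the event cancels, so the apparent risk ratio is the ketorolac fraction divided by the control fraction.

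| Endpoint | f | Control | Ketorolac | Apparent risk ratio |
|---|---|---|---|---|
| Re-intubation | 0.3 | 0.851 | 0.913 | 1.07 |
| Re-intubation | 0.5 | 0.805 | 0.886 | 1.10 |
| Re-intubation | 1.0 | 0.690 | 0.818 | 1.19 |
| Delirium | 0.3 | 0.861 | 0.919 | 1.07 |
| Delirium | 0.5 | 0.815 | 0.892 | 1.09 |
| Delirium | 1.0 | 0.698 | 0.823 | 1.18 |
| Sternal infection, debridement | 0.3 | 0.925 | 0.957 | 1.03 |
| Sternal infection, debridement | 0.5 | 0.875 | 0.929 | 1.06 |
| Sternal infection, debridement | 1.0 | 0.750 | 0.857 | 1.14 |

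At f = 1 the control patients out of reach are 1 − 0.75×0.92 = 31.0% for re-intubation and 1 − 0.75×0.931 = 30.2% for delirium. Independence matters little. With no overlap the ratios at f = 1 are (1 − 0.33×0.571)/(1 − 0.33) = 1.21 and (1 − 0.319×0.571)/(1 − 0.319) = 1.20. With full overlap both are 0.857/0.75 = 1.14.

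**Size against noise.** At an assumed 50% delirium risk and f = 1, the incidences are 0.5×0.698 = 34.9% and 0.5×0.823 = 41.2%, a difference of 6.3 points. With 60 per arm the standard error is √[(0.349×0.651 + 0.412×0.588)/60] = 8.8 points, so the artefact is 0.7 standard errors.

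**Break-even.** At f = 1 the artefact cancels a true relative reduction of 1 − 0.690/0.818 = 16% for re-intubation and 1 − 0.698/0.823 = 15% for delirium.

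**Deletion route.** In Table 1 haematology is due at eight timepoints. A death between days 7 and 30 loses two of them, or 25%. If visits after death count as missing, such a patient passes the 10% limit on that item. The mechanical deficit above then largely disappears. Real events before death are also lost, and the retained groups are no longer those randomised. The documents do not show which way that selection would push the result.

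**The case against.** Several objections have force.

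- **Silence.** Handling of death in secondary endpoints is often left to an analysis plan, which is not at hand, and the article does not say outright that deaths count as complication-free. Silence alone would not be a finding. The point rests on what the article does fix: plain percentages by chi-square or Fisher, no intention-to-treat analysis, and deletion above 10% missing data.
- **Cannot score.** A reader might infer that every death, tracheotomy and neurological injury is barred from scoring an event. The documents do not support this. Death can follow re-intubation, delirium or infection, and tracheotomy can follow re-intubation. Neurological impairment is not defined as coma. Only patients who die or stay ventilated before the event is possible are affected, and no rate is given for them. Even the lower scenarios relax this for deaths only.
- **About 30% of controls.** That figure fits two separate pairs, death with tracheotomy and death with neurological impairment. The three rates together give 1 − 0.75×0.92×0.931 = 35.8% under independence, within a possible range of 25.0% to 39.9%. The article states no joint rate.
- **Direction.** The artefact is zero if the sickest patients have the complication as often as the rest, and it reverses if they have it more often. With a 35.8% share scoring at an assumed 40% against 20% in the rest, the incidences are 27.2% for control and 24.1% for ketorolac.
- **Stakes.** These are a few items in a long secondary list. Death and tracheotomy are already in the primary endpoint, where their difference between arms can be read.

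What survives is that neither route under the stated rules separates survival from the complication.

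**Conclusion.** The point holds as a risk of bias in four secondary comparisons. If early deaths and never-extubated patients are counted as event-free and the drug does nothing to the complication itself, the apparent risk ratio for re-intubation and delirium is about 1.07 to 1.10 with 30% to 50% of deaths first. It is 1.18 to 1.19 as the upper case, with all deaths first, independence and the planned 70% to 40% ratio applied to each component. For sternal infection and debridement, where only death competes, the same scenarios give 1.03 to 1.06 and 1.14.

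A reader might conclude that a drug that keeps patients alive must look worse on these endpoints. That is too strong. The artefact is about 0.7 standard errors in the worked upper case for delirium. A true reduction larger than about 15% to 16% would still show as a benefit in re-intubation and delirium. The problem also changes character if early deaths are deleted. The primary endpoint is not affected by this point.

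**What to change.** In Secondary endpoints and Statistical methods {20a}, for re-intubation, delirium, sternal infection and debridement:

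1. Analyse all randomised patients, and state that death does not lead to deletion under {20c}.
2. Beside each plain incidence, report the event or death before the event could occur. For re-intubation, also count tracheotomy without prior extubation.
3. Tabulate the components of each added composite by arm.
4. Show per arm the number never extubated and the number never assessable for delirium.

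The cost is a few lines of text, best settled before unblinding. Death, tracheotomy, neurological impairment and re-intubation are already outcomes, and Table 1 records complications at every postoperative visit, so no new visits or patients are needed. The downside is small: the added composites mix death, already in the primary endpoint, with the complication. They should therefore stand beside the plain incidences and not replace them.

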## Safety assessment

Ketorolac has been used in clinical practice for many years and is generally well tolerated. According to the medication instructions, the primary adverse reactions associated with ketorolac are gastrointestinal reactions, gastric bleeding, and potential liver and kidney damage. Guidelines from the AHA suggest that ketorolac may also contribute to hypertension and kidney damage [16]. And some cardiovascular adverse events related to ketorolac should be included. Therefore, the safety assessment variables include death, organ malperfusion syndrome, hypertension (blood pressure > 140/90 mmHg), stage 2 AKI diagnosed by KIDGO criteria [18], tracheotomy, neurological impairment prior to discharge, postoperative mechanical circulation support, and postoperative cardiac arrest.

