## Introduction

### Background and rationale {6a}

Acute type A aortic dissection (aTAAD) is considered the most perilous form of aortic disease [1]. Common causes include hypertension, medial degeneration (cystic medial necrosis), and Marfan syndrome [2]. Currently, rapid surgical reconstruction remains the primary treatment option for aTAAD [3–6]. Based on reported references, the in-hospital mortality rate after surgery stands at 25% [7]. Consequently, there is a pressing need to investigate alternative approaches that can effectively decrease surgical mortality.

Previous studies have shown that activated macrophages in mice secrete inflammatory factors, which can enhance migration and invasion capabilities, accelerate degradation of the aortic media, and contribute to the development of type A aortic dissection (TAAD) [8–10]. Additionally, Rho GTPase, an important regulator of cytoskeleton actin and intracellular signal transduction, has been found to be activated in TAAD [11, 12]. In the literature, it has been observed that ketorolac, a nonsteroidal anti-inflammatory drug and inhibitor of the Rho GTPase signaling pathway, can reduce the progression, incidence, and severity of aortic disease in animal models [13, 14].

Previous clinical research has suggested that ketorolac may reduce postoperative mortality, neurological complications, renal complications, and respiratory failure in patients undergoing open abdominal aortic aneurysm replacement surgery [15]. However, it is important to note that this study was retrospective and focused specifically on abdominal aortic aneurysm. Additionally, the 2022 American Heart Association (AHA) guidelines have reported controversy regarding the use of ketorolac in the analgesic treatment of aTAAD [16]. Therefore, our plan is to conduct a single-center, randomized, double-blinded, and placebo-controlled trial to investigate the safety and efficacy of ketorolac in improving the prognosis of aTAAD patients.

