### Intervention description {11a}

The surgeries will be performed by [name]. The study will commence on the day the patients sign an informed consent form and receive their randomized numbers. The ketorolac group, consisting of patients with aTAAD, will be treated with ketorolac. They will receive a preoperative intramuscular injection of 60 mg per 2 ml ketorolac and a postoperative injection of 30 mg per 1 ml ketorolac BID for two consecutive days. The placebo group, also consisting of patients with aTAAD, will receive placebo treatment. They will receive a preoperative intramuscular injection of 2 ml 0.9% saline placebo and a postoperative injection of 1 ml 0.9% saline placebo BID for two consecutive days. During the administration of ketorolac, patients’ blood pressure and renal function will be routinely monitored, and targeted treatment methods such as sedation, hypotension, diuresis, and dialysis will be applied as necessary. Additionally, all included patients will receive the same medical and surgical treatments in accordance with the diagnosis and treatment guidelines for aTAAD. Aortic dissection tissue samples will be collected for laboratory study during the surgery. Both the ketorolac group and the placebo group patients will undergo follow-up examinations before surgery and on the 1st, 3rd, 5th, 7th, 30th, and 90th day after surgery. These examinations will include assessments of adverse drug events, cardiac ultrasound, chest X-ray, laboratory tests (blood routine examination, blood biochemistry, erythrocyte sedimentation rate, coagulation function, CK-MB, cardiac troponin I (cTnI), PCT, IL-6, CRP, myohemoglobin (MYO), type B natriuretic peptide (BNP), D-dimer, etc.) and clinical biomarkers (matrix metalloproteinase-9 (MMP-9), MMP-2, MMP-3, MMP-13, type III procollagen, etc.). CTA examination of the cervical, thoracic, and abdominal aorta artery will be performed before surgery and on the 30th and 90th days after surgery.

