## Discussion

This study presents the first randomized, double-blinded, and placebo-controlled trial conducted to evaluate the safety and efficacy of ketorolac in the treatment of aTAAD. The findings of this trial will serve as a valuable reference for the use of ketorolac in the treatment of aTAAD. If the hypothesis of this trial proves to be accurate, ketorolac treatment for aTAAD can be considered safe and potentially beneficial in reducing inflammatory biomarkers, such as IL-6, CRP, and PCT.

The guidelines state that ketorolac can increase hypertension and cause renal dysfunction, so patients with acute aortic syndrome should use it with caution [16]. However, the guidelines only mention aortic disease and do not specifically address the potential harm of ketorolac in aTAAD. There is also no clear literature support provided. Previous clinical studies have shown that ketorolac is safe for perioperative treatment of surgery [26], and it has also been found to be beneficial in the treatment of aTAAD [15]. Our preliminary basic experiments have confirmed the beneficial effects of ketorolac on animal aortic aneurysms, which align with the conclusions of published basic research papers [12, 27, 28]. From a clinical application perspective, patients in the ICU undergo strict monitoring of their blood pressure, urine output, etc. Active treatment methods can effectively control the hypertension and kidney damage that are concerning in the guidelines. Therefore, the use of ketorolac in the treatment of aTAAD remains a controversial issue.

We intend to reevaluate the safety and efficacy of ketorolac in the treatment of aTAAD. Our approach involves two main components: Firstly, we will conduct a randomized controlled trial. Secondly, we will collect aortic tissue samples from patients during surgery and perform a series of laboratory experiments to investigate the underlying mechanisms and pathways. By integrating both clinical trials and basic experiments, our study aims to offer scholars a solid reference framework and novel insights.

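### The only named blood-pressure safety variable is a fixed threshold that ignores the pre-dose value and antihypertensive treatment, so it is less sensitive than the data already collected allow

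*Protocol article*

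**What the plan says.** The Safety assessment section gives its reason first: "Guidelines from the AHA suggest that ketorolac may also contribute to hypertension and kidney damage". It then lists eight safety variables, among them "hypertension (blood pressure > 140/90 mmHg". No baseline value, change, time window or treatment status is attached to that item. It is the only blood-pressure outcome the article names; the primary and secondary endpoint lists under Outcomes {12} contain none.

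Other sections bear on it:

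- Background and rationale {6a}: "Common causes include hypertension, medial degeneration (cystic medial necrosis), and Marfan syndrome". Eligibility criteria {10} excludes Marfan syndrome but not hypertension.
- Intervention description {11a}: during dosing "blood pressure and renal function will be routinely monitored", and "targeted treatment methods such as sedation, hypotension, diuresis, and dialysis will be applied as necessary". In this context the word hypotension is read here as blood-pressure lowering.
- Discussion: "Active treatment methods can effectively control the hypertension and kidney damage that are concerning in the guidelines".
- Table 1: vital signs are marked at enrolment, during surgery and on postoperative days 1, 3, 5, 7, 30 and 90. The enrolment column comes before the allocation column, where the first dose is marked, so a pre-dose value is scheduled.
- Statistical methods {20a}: for categorical variables, "frequency will be expressed as percentages and analyzed using the chi-square test or Fisher’s exact test", with no adjustment for baseline.

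**The concern.** The variable is there to show whether ketorolac raises blood pressure. On its natural reading, a bare threshold asks only whether a patient is above the line. Someone already above it before dosing has nowhere further to go, and counts the same in both arms however much the pressure rises. Someone whose pressure rises but is treated back below the line is not counted either. Both features pull the two arms together.

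Safety is half of the stated objective, and blood pressure is one of the two harms the article takes from the guideline. The Discussion presents the trial as a re-evaluation against that caution. A finding of no difference on an insensitive variable would be weak evidence of no harm.

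**Working it through.** **The plan's own figure.** The article gives no figure for blood pressure. Its sample size concerns the efficacy composite (70% v 40%) and is reproduced here only to fix n. With unpooled variance, two-sided 0.05 and 90% power: (1.960 + 1.282)² × (0.7×0.3 + 0.4×0.6) / 0.3² = 52.5, so 53 per arm as stated. A loss of 11% gives 53/0.89 = 59.6, so 60 per arm as stated.

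**Inputs.** From the article: 60 per arm, two-sided 0.05. Assumed, because the article has no blood-pressure data: a true shift of 10 mmHg remaining after any treatment, SD 15 or 20 mmHg, one normally distributed reading per patient, correlation with baseline r = 0.3 to 0.7, and a control-arm rate above the threshold from 10% to 95%.

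**Formulas.**

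- Ketorolac rate: p1 = Φ(Φ⁻¹(p0) + shift/SD).
- Threshold power: Φ[(p1 − p0 − 1.960 × SE0)/SE1], with SE0 from the pooled rate and SE1 from the separate rates.
- Mean power: Φ[shift/(SD × √(2/60)) − 1.960], with SD multiplied by √(1 − r²) when adjusted for baseline.

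**Worked case, p0 = 50%, SD 15.** p1 = Φ(0 + 0.667) = 0.7475. SE0 = √(2 × 0.624 × 0.376/60) = 0.0885. SE1 = √((0.250 + 0.189)/60) = 0.0855. Power = Φ[(0.2475 − 0.1734)/0.0855] = Φ(0.867) = 80.7%.

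**Worked case, adjusted mean, SD 20, r = 0.3.** Residual SD = 20 × √0.91 = 19.08. Power = Φ[10/(19.08 × 0.1826) − 1.960] = Φ(0.911) = 81.9%.

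| Measure, 10 mmHg shift, 60 per arm | Power, SD 15 | Power, SD 20 |
|---|---|---|
| Threshold, control rate 10% | 67.0% | 41.9% |
| Threshold, 30% | 81.9% | 56.9% |
| Threshold, 50% | 80.7% | 57.2% |
| Threshold, 70% | 70.0% | 48.6% |
| Threshold, 90% | 38.7% | 27.1% |
| Threshold, 95% | 24.3% | 17.9% |
| Mean, unadjusted | 95.5% | 78.2% |
| Mean, adjusted, r = 0.3 | 96.9% | 81.9% |
| Mean, adjusted, r = 0.5 | 98.8% | 88.5% |
| Mean, adjusted, r = 0.7 | 99.9% | 97.0% |

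**Ceiling.** At a control rate of 90%, power is only about 72% even if nearly every ketorolac patient is above the line; at 95% it is about 42%.

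**Sensitivity.** With 53 evaluable per arm, the threshold has 52–77% power at control rates of 30–50% and 16–35% at 90–95%, against 77–99.8% for the adjusted mean. For a 5 mmHg shift at 60 per arm, the threshold has about 8–30% over all the control rates, the unadjusted mean 28–45% and the adjusted mean 30–73%.

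At the same SD, the measured value beats the threshold at every control rate. Much of the gain comes from using the measurement itself, and baseline adjustment adds to it.

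**The case against.** The strongest reply is that the article gives no rate above 140/90 mmHg in either arm. A common cause of dissection is a statement about aetiology, not about pressure at trial visits, and active lowering of pressure could keep the control rate low or moderate. This stands. A reader might infer that most patients will cross the line whatever they receive, so that the variable can hardly detect harm. The article does not support that: at control rates of 30–50% the threshold keeps 57–82% power for a 10 mmHg shift.

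A reader might also infer that the plan discards the measured pressures. It does not say so. The safety list is introduced as what the variables include, Statistical methods {20a} covers continuous variables, and adverse events are graded by CTCAE, so hypertension reported as an adverse event would carry a grade. Whether a pre-existing high reading counts as an event is not spelled out.

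It can be said too that time windows and covariates belong in a full protocol or analysis plan, which is not shown. That answers a complaint about missing detail. Here, however, the article does fix a definition, and a better use of already scheduled data is available.

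Finally, treatment to target would also mask a difference in means, and pressure before emergency surgery may correlate only weakly with later values. Both stand. The first is why antihypertensive use must be reported alongside. On the second, even the unadjusted mean has 78–96% power.

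**Conclusion.** The point holds as a loss of sensitivity whose size cannot be fixed from the article. For an assumed 10 mmHg shift and SD 15–20 mmHg at 60 per arm, the threshold has about 57–82% power at control rates of 30–50% and 18–39% at 90–95%. A baseline-adjusted mean has 82–99.9% for r of 0.3 to 0.7. Shift, SD, correlation and control rate are all assumptions.

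Three limits apply. Randomisation balances baseline hypertension on average, so inferring bias between arms would be wrong. The variable is one of eight supporting safety variables, so neither the primary nor the secondary endpoints are affected. And for a shift near 5 mmHg the trial is too small for any of these measures to be reliable, so part of the weakness there is sample size and not the definition.

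**What to change.** Add one prespecified safety analysis: the between-arm difference in systolic and in diastolic pressure over the dosing and early postoperative visits in Table 1, adjusted for the pre-dose value and reported with 95% confidence intervals. Report antihypertensive use by arm beside it, because treatment can mask a difference in either measure. Keep the stated threshold as a descriptive count by arm, split into patients already above it at baseline and patients newly above it.

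The vital signs are already scheduled; antihypertensive use by arm would have to be tabulated if that is not already planned. No threshold, dose or treatment rule changes. The cost is a few lines of analysis text and one more model to report.
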